# Pyrotinib combined with thalidomide in advanced non-small-cell lung cancer patients harboring HER2 exon 20 insertions (PRIDE): protocol of an open-label, single-arm phase II trial

**DOI:** 10.1186/s12885-021-08759-8

**Published:** 2021-09-16

**Keywords:** Pyrotinib, Thalidomide, Non-small-cell lung cancer, Human epidermal growth factor receptor 2, Protocol

## Abstract

**Background:**

Standard therapy for human epidermal growth factor receptor 2 (HER2)-mutant non-small-cell lung cancer (NSCLC) is lacking. The clinical benefits with pan-HER inhibitors (afatinib, neratinib, and dacomitinib), anti-HER2 antibody drug conjugate (ADC) trastuzumab emtansine, and an emerging irreversible tyrosine kinase inhibitor (TKI) poziotinib were modest. Another new ADC trastuzumab deruxtecan showed encouraging outcomes, but only phase I study was completed. Pyrotinib, another emerging irreversible epidermal growth factor receptor (EGFR)/HER2 dual TKI, has been approved in *HER2*-positive breast cancer in 2018 in China. It has shown promising antitumor activity against *HER2*-mutant NSCLC in phase II trials, but pyrotinib-related diarrhea remains an issue. The antiangiogenic and immunomodulatory drug thalidomide is a cereblon-based molecular glue that can induce the degradation of the IKAROS family transcription factors IKZF1 and IKZF3. The use of thalidomide can also decrease gastrointestinal toxicity induced by anti-cancer therapy.

**Methods:**

This is an open-label, single-arm phase II trial. A total of 39 advanced NSCLC patients with *HER2* exon 20 insertions and ≤ 2 lines of prior chemotherapy will be recruited, including treatment-naïve patients who refuse chemotherapy. Patients are allowed to have prior therapy with immune checkpoint inhibitors and/or antiangiogenic agents. Those who have prior HER2-targeting therapy or other gene alterations with available targeted drugs are excluded. Eligible patients will receive oral pyrotinib 400 mg once daily and oral thalidomide 200 mg once daily until disease progression or intolerable toxicity. The primary endpoint is objective response rate.

**Discussion:**

The addition of thalidomide to pyrotinib is expected to increase the clinical benefit in advanced NSCLC patients with *HER2* exon 20 insertions, and reduce the incidence of pyrotinib-related diarrhea. We believe thalidomide is the stone that can hit two birds.

**Trial registration:**

ClinicalTrials.gov Identifier: NCT04382300. Registered on May 11, 2020.

## Background

Mutations in human epidermal growth factor receptor 2 (HER2, neu or ERBB2) are found in approximately 2–6.7% of patients with non-small-cell lung cancer (NSCLC) [1–3], and the median overall survival (OS) in this subpopulation is around 22.9 months from the diagnosis of metastatic disease [1]. This mutation is prone to be found in non-smokers and females, and the histological type is more likely to be adenocarcinoma or adenosquamous carcinoma [4–7]. During the past few years, various HER2-targeting therapeutic strategies for *HER2*-mutant NSCLC were developed, including pan-HER inhibitors (afatinib, neratinib, and dacomitinib) [8–10], anti-HER2 antibody drug conjugates (ADCs; such as trastuzumab emtansine [T-DM1]) [11], and emerging irreversible tyrosine kinase inhibitors (TKIs; such as poziotinib) [12]. However, the clinical benefits with these drugs were modest, with the objective response rate (ORR) of 4–44% and median progression-free survival (PFS) of 3.0–5.6 months [8–12]. The new ADC trastuzumab deruxtecan (DS-8201a) brought encouraging clinical benefits for *HER2*-mutant NSCLC. The ORR and median PFS were 73% (8/11) and 11.3 months with trastuzumab deruxtecan in patients with *HER2*-mutant NSCLC, respectively [13]. However, only exploratory phase I results of this novel potent drug were reported at present. Until now, chemotherapy is still the stand of care for this population, and novel treatment strategy is urgently needed.

Pyrotinib is an oral, irreversible epidermal growth factor receptor (EGFR)/HER2 dual TKI. The combination of pyrotinib with capecitabine has been approved for the treatment of patients with *HER2*-positive, relapsed or metastatic breast cancer who were previously treated with taxanes, anthracyclines, and/or trastuzumab in China [14]. In a *HER2* exon 20 insertion patient-derived xenografts model, a more profound tumor regression was observed with pyrotinib than with afatinib and T-DM1 [15]. Two phase II trials have demonstrated the promising antitumor activity and acceptable safety profile of pyrotinib monotherapy in patients with previously treated, *HER2*-mutant advanced NSCLC, with the ORR of 53% (8/15) and 30% (18/60), and median PFS of 6.4 and 6.9 months, respectively [15, 16]. A multicenter, randomized phase III trial (NCT04447118) has been started to compare the efficacy and safety of pyrotinib versus docetaxel in patients with advanced non-squamous NSCLC harboring *HER2* exon 20 mutations who failed platinum-based chemotherapy. However, pyrotinib-related diarrhea remains an issue, with the incidence of 27% (4/15) and 92% (55/60) in previous phase II trials [15, 16]. Thus, we wanted to explore a combination regimen to further enhance the antitumor activity and improve the safety and tolerability of pyrotinib in advanced NSCLC patients with *HER2* exon 20 insertions.

Thalidomide, a derivative of glutamic acid, is an antiangiogenic and immunomodulatory drug. It has been extensively used in patients with multiple myeloma for decades [17, 18]. These years, thalidomide has been proved to be one of the molecular glues that can induce the protein degradation of undruggable targets, which can compromise the limitation of inhibitors [19]. By binding cereblon (CRBN), thalidomide can activate the E3 ubiquitin ligase CRL4^CRBN^-mediated ubiquitination and degradation of the IKAROS family transcription factors IKZF1 and IKZF3 [19], which play key roles in the tumorigenesis and progression of hematologic malignancies [20]. For solid cancers, the clinical activity of thalidomide monotherapy is limited [21], but recent in vitro studies demonstrated the synergistic effects of thalidomide in combination with TKIs on NSCLC [22, 23]. A pilot study of thalidomide plus erlotinib in 52 advanced NSCLC patients with acquired resistance to erlotinib indicated the reversion effect of thalidomide on TKI-acquired resistance [24]. In addition to the antiangiogenic and immunomodulatory actions, the characteristic of thalidomide as a molecular glue may contribute to the synergistic effect in solid cancers. On the other hand, a striking absence of diarrhea was observed when thalidomide was added to chemotherapy [25, 26]. Thus, we hypothesized that the addition of thalidomide to pyrotinib might increase the clinical benefit and reduce the incidence of pyrotinib-related diarrhea.

Therefore, this PRIDE study is conducted to investigate the efficacy and safety of pyrotinib combined with thalidomide in advanced NSCLC patients with *HER2* exon 20 insertions.

## Methods/design

### Study design

This is a single-center, open-label, single-arm phase II trial (ClinicalTrials.gov Identifier: NCT04382300) in advanced NSCLC patients with *HER2* exon 20 insertions (Fig. 1). The study is being conducted in accordance with the Declaration of Helsinki and Good Clinical Practice. The protocol and its amendments have been approved by the ethics committee of Shanghai Chest Hospital (No. LS2003). The recruitment was started on May 25, 2020, and the first patient was recruited on June 24, 2020. The enrolment is estimated to be completed in December 2021 for the first stage and in December 2022 for the second stage.

### Eligibility criteria

The patient inclusion and exclusion criteria are detailed in Table 1.

**Table 1 Tab1:** Eligibility criteria

**Inclusion criteria**	
1	Aged 18–80 years
2	ECOG performance status 0–1
3	Life expectancy ≥3 months
4	At least one measurable lesion according to RECIST 1.1 [27]
5	Histologically or cytologically proved stage IIIB/IV NSCLC according to the 7th edition of TNM classification and staging system for lung cancer published by IASLC [28]
6	*HER2* exon 20 insertions confirmed by next generation sequencing or polymerase chain reaction (if blood samples are used, the mutation abundance should be ≥10%)
7	Disease progression during or after platinum-based chemotherapy, or refusing chemotherapy (patients are allowed to have prior therapy with PD-1/PD-L1 inhibitors and/or antiangiogenic agents)
8	No more than two prior chemotherapy regimens (a. replacing platinum drug due to toxicity is considered as a new regimen; b. adjuvant chemotherapy is not considered as a prior regimen if disease recurrence occurred at more than 6 months after the last dose)
9	No radiotherapy within 3 months, or prior radiotherapy with radiation area < 25% of bone marrow area at least 4 weeks before enrollment
10	Adequate organ function with the following criteria: (a) neutrophil count ≥1.5 × 10^9^/L; platelet count ≥90 × 10^9^/L; Hb ≥90 g/L (b) INR ≤1.5; APTT ≤1.5 × ULN (c) total bilirubin ≤1.5 × ULN; ALT and AST ≤2 × ULN for liver metastases (d) BUN and creatinine ≤1.5 × ULN; creatinine clearance rate ≥ 50 mL/min (e) LVEF ≥50%; QTcF < 470 ms for female and < 450 ms for male patient
11	Willingness to use highly effective contraception from the start of the study to 90 days after the last dose of study drug
12	Written informed consent

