**Exclusion criteria**	
1	Prior HER2-targeting therapy before enrollment, including but not limited to trastuzumab, lapatinib, pyrotinib, and neratinib
2	Other gene alterations with available targeted drugs, such as *EGFR* mutations, *T790M* resistance mutations, *ALK* fusions, *ROS1* fusions, *RET* rearrangements, *BRAF V600E* mutations, *NTRK* fusions, and *MET* exon 14 skipping
3	Factors influencing the oral administration of drugs, such as inability to swallow, chronic diarrhea, intestinal obstruction, or other gastrointestinal diseases or abnormalities
4	The third-space effusion, such as pleural effusion, ascites and pericardial effusion, which cannot be controlled by drainage or other methods
5	Radiotherapy, chemotherapy, surgery, or other targeted therapy for non-small-cell lung adenocarcinoma within 4 weeks
6	Active brain metastases, meningeal metastases, spinal compression, or CT or MRI revealing brain or leptomeningeal diseases at screening (patients with symptomatically stable brain metastases can be enrolled if no cerebral hemorrhage is found by brain MRI, CT or venography)
7	Uncontrolled hypokalemia or hypomagnesemia
8	Allergy history to the components of study drug
9	History of immunodeficiency disease (including positive test of human immunodeficiency virus, active hepatitis B/C, or other acquired or congenital immunodeficiency disease) or organ transplantation
10	History of cardiac diseases, including angina, arrhythmia requiring drug therapy or of clinical significance, myocardial infarction, heart failure, and other cardiac diseases unsuitable for this trial as judged by the investigator
11	Thrombotic disease or history of thrombus
12	Other malignancies within 5 years, except for cured cervical cancer in situ, skin basal cell cancer, and skin squamous cell cancer
13	History of neurological or mental disorders, such as epilepsy and dementia
14	Respiratory syndrome (dyspnea ≥grade 2 using NCI CTCAE 5.0)
15	Coagulation disorders (INR > 1.5, prothrombin time > ULN + 4 s, or APTT > 1.5 × ULN), with bleeding tendency or receiving thrombolytic or anticoagulant therapy
16	Renal dysfunction (urine protein ≥++, or 24-h proteinuria ≥1.0 g)
17	Participating in other clinical trials within 4 weeks
18	Pregnant or lactating woman
19	Concomitant diseases seriously affecting the patient safety or the completion of study as judged by the investigator, such as uncontrolled severe hypertension, severe diabetes mellitus, and active infection

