20	Any other condition unsuitable for the study as judged by the investigator

*ECOG* Eastern Cooperative Oncology Group, *RECIST* Response Evaluation Criteria In Solid Tumors, *NSCLC* non-small-cell lung cancer, *IASLC* International Association for the Study of Lung Cancer, *PD-1* programmed death-1, *PD-L1* programmed death-ligand 1, *Hb* hemoglobin, *INR* international normalized ratio, *APTT* activated partial thromboplastin time, *ULN* upper limit of normal, *ALT* alanine transaminase, *AST* aspartate transaminase, *BUN* blood urea nitrogen, *LVEF* left ventricular ejection fraction, *QTcF* QT interval corrected by Fridericia’s formula, *CT* computed tomography, *MRI* magnetic resonance imaging, *NCI CTCAE* National Cancer Institute Common Terminology Criteria for Adverse Events

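### The only ALT/AST entry limit, as printed in Table 1, applies to patients with liver metastases; eligible patients without them have no stated ceiling

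*Protocol article*

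**What the plan says.** Under Eligibility criteria, the protocol article points to a single source for the entry rules: "The patient inclusion and exclusion criteria are detailed in Table 1".

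In that table, inclusion criterion 10 is introduced as "Adequate organ function with the following criteria" and lists items (a) to (e). Item (c), the hepatic item, reads "total bilirubin ≤1.5 × ULN; ALT and AST ≤2 × ULN for liver metastases".

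Inclusion criterion 5 defines the disease population as "Histologically or cytologically proved stage IIIB/IV NSCLC". No criterion requires liver metastases.

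The liver-related exclusion is part of exclusion 9, which covers "active hepatitis B/C, or other acquired or congenital immunodeficiency disease". It gives no enzyme value. The last exclusion is a discretionary one: "Any other condition unsuitable for the study as judged by the investigator".

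**The concern.** The qualifier at the end of 10(c) restricts the ALT/AST limit to one subgroup, and nothing is stated for the rest. This runs the wrong way for a safety rule. It caps the patients whose tumour might explain raised enzymes, and leaves uncapped those in whom a raised value has no such explanation.

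Two things are at stake. Applied literally, the rule would admit a patient without liver metastases at any ALT or AST level, provided the other criteria were met. And a reader of the eventual results could not tell which baseline transaminase levels were allowed, which matters when interpreting enzyme rises on a two-drug combination.

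**Working it through.** There is no formula or planned figure to reproduce; the check is a reading of the text.

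**1. Every place where an ALT/AST limit could stand (protocol article)**

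| Place | What it sets | ALT/AST entry limit? |
|---|---|---|
| Table 1, inclusion 10(c) | 2 × ULN, tied to liver metastases | Yes, one subgroup only |
| Table 1, other inclusion criteria | No transaminase value | No |
| Table 1, exclusions 1 to 20 | Active hepatitis B/C, coagulation disorders, investigator judgement | No |
| Table 1 footnote | Spells out the abbreviations | No |
| Table 2, dose adjustment | Acts after treatment has started | No |

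There is one ALT/AST entry limit, and it is conditional.

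**2. Whether the uncovered group can enter**

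Criterion 5 admits stage IIIB and stage IV disease. Stage IIIB patients, and stage IV patients whose metastases lie elsewhere, are eligible. The uncovered group is therefore not empty by definition.

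**3. Whether the entry looks complete beside its neighbours**

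Parameters in criterion 10:

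- (a) neutrophils, platelets, hemoglobin: 3
- (b) INR, APTT: 2
- (c) bilirubin, ALT, AST: 3
- (d) BUN, creatinine, creatinine clearance: 3
- (e) LVEF, QTcF: 2

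Total: 3 + 2 + 3 + 3 + 2 = 13. Parameters with a limit for one subgroup only: ALT and AST, so 2. Parameters with a limit for every patient: 13 − 2 = 11.

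QTcF counts among the 11. It is also split by subgroup, but both halves are given (470 ms for women, 450 ms for men). ALT and AST show only one half of a split. The line runs straight into item (d) with no redaction mark or visible break.

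**4. What the rule could have been**

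| Reading | Without liver metastases | With liver metastases |
|---|---|---|
| As printed | no limit | ≤2 × ULN |
| A: qualifier is stray | ≤2 × ULN | ≤2 × ULN |
| B: limit for the others was lost | unknown, stricter than 2 × ULN | ≤2 × ULN |
| C: higher limit for liver metastases was lost | ≤2 × ULN | unknown, above 2 × ULN |

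Readings A, B and C all exclude a patient without liver metastases whose ALT is above 2 × ULN; the printed text does not. A, B and C also differ from one another, so the document does not reveal the intended rule.

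**5. What else limits the exposure**

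- At entry, for everyone: bilirubin at most 1.5 × ULN, INR at most 1.5 and APTT at most 1.5 × ULN (criterion 10).
- At entry, by exclusion: active hepatitis B/C (9), coagulation disorders including a prolonged prothrombin time (15), and investigator judgement (19 and 20). Exclusion 15 also mentions bleeding tendency or anticoagulant use, so prothrombin time may not exclude a patient by itself.
- On treatment: Table 2 interrupts and reduces pyrotinib for most non-hematologic events of grade 2 or above, which would include transaminase events. Its printed restart condition refers to recovery from diarrhea, so it gives no enzyme recovery threshold.

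None of these is an ALT/AST limit at entry.

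**The case against.** The strongest reply is that this is a reporting slip and not a fault in the trial. It is unlikely that anyone intended to leave transaminases uncapped. The likeliest explanation is a clause lost when a multi-part laboratory criterion was condensed into one table cell. Patients are enrolled under the full protocol, which the ethics committee approved and which is not shown. The trial has a single center, so sites cannot diverge in how they read the line. The bilirubin and coagulation limits, the hepatitis exclusion and investigator discretion make it improbable that a patient with marked unexplained enzyme elevation would be treated. No affected patient can be identified.

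Most of this stands, and it limits the weight of the point. Nothing here shows that any patient was screened under a faulty rule, and the trial should not be described as lacking a transaminase ceiling. The view that the printed rule runs the wrong way is also a clinical judgement; the article gives no hepatic rationale for either drug.

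What does not stand is that the matter can be left to the fuller document. The article does not omit the criterion; it prints it, in the table it names as the place where eligibility is detailed, with a condition that leaves some eligible patients uncovered. The other safeguards reduce the exposure but do not supply the missing limit.

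**Conclusion.** The point holds for the rule as printed. Criterion 10(c) gives an ALT/AST limit for one subgroup only, and eligible patients without liver metastases have none: 2 of the 13 parameters in criterion 10 are affected.

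The number of patients involved cannot be derived. It lies between 0 and the full sample of 39, and may well be 0. The primary endpoint, the two-stage design (19 + 20 = 39) and its error rates are unaffected.

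This is a minor eligibility and safety correction, but it should be made because it concerns an operative entry rule. The conclusion rests on taking the printed wording at face value. If the approved protocol states a limit for all patients, the defect is confined to the article.

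**What to change.** Check 10(c) against the ethics-approved protocol and correct Table 1 so that it states two things explicitly: the ALT/AST limit for patients without liver metastases and the limit for patients with them. If one value applies to all, remove the qualifier.

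If the approved protocol has the same wording, amend it so that patients without liver metastases also have a ceiling. The sponsor must set the value; this document does not settle it.

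The cost is a one-line correction to the table, plus a protocol amendment only in the second case. Sample size and error rates do not change.

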**Exclusion criteria**	
1	Prior HER2-targeting therapy before enrollment, including but not limited to trastuzumab, lapatinib, pyrotinib, and neratinib
2	Other gene alterations with available targeted drugs, such as *EGFR* mutations, *T790M* resistance mutations, *ALK* fusions, *ROS1* fusions, *RET* rearrangements, *BRAF V600E* mutations, *NTRK* fusions, and *MET* exon 14 skipping
3	Factors influencing the oral administration of drugs, such as inability to swallow, chronic diarrhea, intestinal obstruction, or other gastrointestinal diseases or abnormalities
4	The third-space effusion, such as pleural effusion, ascites and pericardial effusion, which cannot be controlled by drainage or other methods
5	Radiotherapy, chemotherapy, surgery, or other targeted therapy for non-small-cell lung adenocarcinoma within 4 weeks
6	Active brain metastases, meningeal metastases, spinal compression, or CT or MRI revealing brain or leptomeningeal diseases at screening (patients with symptomatically stable brain metastases can be enrolled if no cerebral hemorrhage is found by brain MRI, CT or venography)
7	Uncontrolled hypokalemia or hypomagnesemia
8	Allergy history to the components of study drug
9	History of immunodeficiency disease (including positive test of human immunodeficiency virus, active hepatitis B/C, or other acquired or congenital immunodeficiency disease) or organ transplantation
10	History of cardiac diseases, including angina, arrhythmia requiring drug therapy or of clinical significance, myocardial infarction, heart failure, and other cardiac diseases unsuitable for this trial as judged by the investigator
11	Thrombotic disease or history of thrombus
12	Other malignancies within 5 years, except for cured cervical cancer in situ, skin basal cell cancer, and skin squamous cell cancer
13	History of neurological or mental disorders, such as epilepsy and dementia
14	Respiratory syndrome (dyspnea ≥grade 2 using NCI CTCAE 5.0)
15	Coagulation disorders (INR > 1.5, prothrombin time > ULN + 4 s, or APTT > 1.5 × ULN), with bleeding tendency or receiving thrombolytic or anticoagulant therapy
16	Renal dysfunction (urine protein ≥++, or 24-h proteinuria ≥1.0 g)
17	Participating in other clinical trials within 4 weeks
18	Pregnant or lactating woman
19	Concomitant diseases seriously affecting the patient safety or the completion of study as judged by the investigator, such as uncontrolled severe hypertension, severe diabetes mellitus, and active infection
20	Any other condition unsuitable for the study as judged by the investigator

*ECOG* Eastern Cooperative Oncology Group, *RECIST* Response Evaluation Criteria In Solid Tumors, *NSCLC* non-small-cell lung cancer, *IASLC* International Association for the Study of Lung Cancer, *PD-1* programmed death-1, *PD-L1* programmed death-ligand 1, *Hb* hemoglobin, *INR* international normalized ratio, *APTT* activated partial thromboplastin time, *ULN* upper limit of normal, *ALT* alanine transaminase, *AST* aspartate transaminase, *BUN* blood urea nitrogen, *LVEF* left ventricular ejection fraction, *QTcF* QT interval corrected by Fridericia’s formula, *CT* computed tomography, *MRI* magnetic resonance imaging, *NCI CTCAE* National Cancer Institute Common Terminology Criteria for Adverse Events

**Fig. 1 Fig1:**
[figure not shown]
Study design

### *HER2* mutation confirmation

*HER2* exon 20 insertions will be confirmed by next generation sequencing, amplification refractory mutation system-polymerase chain reaction, or droplet digital polymerase chain reaction. Tumor tissues obtained from biopsy or circulating tumor DNA from blood samples can be used for HER2 testing. If blood samples are used, the mutation abundance should be ≥10%. The gene mutation reports from other testing organizations are allowed.

